## Abstract

**Background:**

Sleep, physical activity, and diet are key determinants of health, each independently associated with chronic disease risk and mortality. These behaviors also interact: insufficient sleep can impair physical activity and dietary choices, while regular exercise and healthy diet promote better sleep. Although lifestyle interventions commonly target physical activity and diet, few simultaneously address sleep. Emerging evidence suggests that even small improvements across all three behaviors can reduce all-cause mortality, highlighting the potential of multi-behavior approaches. However, the effects of a lifestyle intervention simultaneously targeting sleep, physical activity, and diet on quality of life and physical activity levels in inactive adults remain largely unexplored.

**Methods:**

The SPIRAL+ study is a single-center, randomized controlled trial conducted in France, among non-exercising adults aged 18–80 years. Participants (*n* = 201) will be randomized to one of three groups: (1) lifestyle intervention (physical activity and diet) (2), lifestyle plus sleep intervention, or (3) control. Assessments will be conducted at baseline, 6 months (post-intervention), and 12 months. The primary outcomes are health-related quality of life (EQ-5D-5 L) and daily step count (measured by accelerometer) assessed immediately after the 6-month intervention. Secondary outcomes include whether intervention effects are sustained at 12 months, along with markers of physical fitness (cardiorespiratory fitness, body composition, handgrip strength), physical activity and sedentary behavior (accelerometry), and sleep (home-based sleep test, actigraphy, and validated questionnaires). Additional self-reported outcomes will cover diet, mental wellbeing, motivation, quality of life, and psychological constructs related to health behavior change. A qualitative component will explore barriers and facilitators to adherence through semi-structured interviews.

**Discussion:**

This trial will evaluate whether adding a sleep component to a lifestyle intervention improves quality of life and physical activity levels in inactive adults. If effective, the findings will support the integration of sleep into multi-behavior interventions to enhance health outcomes and inform future public health strategies.

**Trial registration:**

Clinical Trials NCT06424847.

**Supplementary Information:**

The online version contains supplementary material available at 10.1186/s12889-026-26959-4.

## Introduction

Sufficient sleep, regular physical activity, and a balanced diet are fundamental pillars of health and well-being, each contributing to the prevention of chronic diseases and premature mortality [1, 2].

Inadequate sleep has been linked to metabolic and cognitive dysfunction, driven by mechanisms such as insulin resistance, inflammation, and dysregulation of appetite-related hormones [3, 4]. Physical inactivity is a well-established risk factor for numerous chronic conditions [1], while meeting physical activity recommendations is associated with a significantly lower risk of all-cause mortality [5, 6]. Similarly, poor dietary habits, including excessive calorie intake and nutrient-poor food choices, contribute to the development of common non-communicable diseases, accelerate biological aging, and increase the likelihood of early mortality [7, 8].

Beyond their individual impact, these three behaviors are intricately linked. Sleep deprivation can lead to reduced physical activity due to fatigue, while engaging in regular exercise has been shown to improve sleep quality [9–11]. Likewise, insufficient sleep disrupts appetite regulation, influencing food intake and dietary choices [12] and, conversely, an unhealthy diet can impair neurotransmitter activity and sleep patterns [13].

Emerging evidence shows that even modest improvements across these domains yield measurable benefits. In a recent prospective cohort, small increases in sleep duration, physical activity, and diet quality were associated with a 10% lower risk of all-cause mortality [14]. These findings highlight the importance of developing effective interventions that simultaneously target these sleep, physical activity and diet to optimize health outcomes.

Previous studies have primarily evaluated lifestyle interventions targeting physical activity and diet in primary prevention. A recent meta-analysis showed that, compared to usual care, such interventions reduced blood pressure, total cholesterol, BMI and waist circumference [15]. Evidence also indicates improvements in health-related quality of life among adults with metabolic syndrome [16]. Interventions focusing on sleep have also been tested; for example, a recent randomized controlled trial combining physical activity and sleep strategies improved sleep quality in middle-aged adults with poor baseline sleep [17]. However, to our knowledge, no study has yet examined the combined effects of an intervention targeting physical activity, diet, and sleep on quality of life and physical activity levels in inactive adults.

Taken together, these findings underscore the need for innovative interventions that move beyond single-behavior approaches and address the interconnected nature of sleep, physical activity, and diet. Designing such multi-component programs requires not only targeting these behaviors simultaneously but also ensuring that participants are supported in adopting and maintaining changes over time. To this end, drawing upon robust theoretical frameworks [18, 19] is essential to guide intervention content, enhance adherence, and maximize the likelihood of sustainable health improvements.

### Theoretical framework

The lifestyle intervention targeting physical activity and diet is grounded in self-determination theory (SDT) and affectivism. SDT highlights the role of autonomous motivation, when behavior is driven by choice, values, or enjoyment, in sustaining long-term engagement [20–23]. By supporting the basic needs for autonomy, competence, and relatedness, the intervention seeks to foster autonomous motivation. In addition, research on affective responses to physical activity indicates that positive experiences, especially at peak and final moments (“peak-end rule”), can shape remembered and anticipated pleasure, reinforcing future participation [24].

The sleep component is informed by the theory of planned behavior (TPB) and the health action process approach (HAPA). TPB emphasizes the role of attitudes, norms, and perceived behavioral control in shaping intentions [25, 26], while HAPA addresses the well-documented intention–behavior gap by integrating self-regulatory processes such as action and coping planning [27]. These frameworks guide the selection of evidence-based behavior change techniques to promote sustainable improvements in sleep health.

### Study objectives

The SPIRAL+ study is designed to address this evidence gap by evaluating the effectiveness of a lifestyle intervention that integrates sleep, physical activity, and diet.

The primary objective of the study is to determine whether adding a structured sleep component to a standard lifestyle program improves health-related quality of life and physical activity (step count) in physically inactive adults, compared to a lifestyle intervention without sleep support. These primary outcomes will be assessed immediately after completion of the 6-month intervention.

The secondary objectives are to examine whether the effects on quality of life and physical activity are sustained at 12 months, to evaluate additional health outcomes such as physical fitness (cardiorespiratory fitness, body composition, handgrip strength), sedentary behavior, sleep quality and duration, dietary habits, mental wellbeing, vitality, and motivational or psychological constructs, and to explore barriers and facilitators to adherence through a qualitative component that includes semi-structured interviews with participants.

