### Outcomes

#### Primary outcome

The study has two primary outcomes, assessed 6 months after randomization:Steps per day, measured objectively using an Actigraph GT3X accelerometer (Actigraph Corp, USA). Steps per day were chosen because increases in daily step count are strongly associated with reduced all-cause mortality [31]. Furthermore, step count is passively tracked by widely used consumer technologies (e.g., smartphones), giving it practical relevance. Recent dose–response evidence also provides insights to inform future physical activity guidelines [32].Health-related quality of life, measured with the EQ-5D-5L questionnaire. This instrument is a widely used, cognitively simple, self-administered measure that assesses five dimensions of health (mobility, self-care, usual activities, pain/discomfort, anxiety/depression), each rated on five severity levels, along with a visual analog scale (EQ-VAS) for overall health [33]. Quality of life was selected as a co-primary outcome because self-rated health and health-related quality of life are robust predictors of mortality and chronic disease risk, and are sensitive to changes in lifestyle behaviors.

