### Sample size calculations

Sample size and power calculations were performed using R statistical software under the following assumptions: balanced randomization (1:1:1 across the three arms); changes in steps per day follow a Gaussian distribution, centered at 0 in the control arm, 1800 in the lifestyle intervention arm, and 2200 in the lifestyle and sleep intervention arm, with a standard deviation of 2121 [45, 46]; changes in EQ-5D-5 L scores follow a Gaussian distribution, centered at 0 in the control arm, 0.07 in the lifestyle intervention arm, and 0.14 in the lifestyle and sleep intervention arm [47], with a standard deviation of 0.21. This 0.07 increase is based on the anticipated observation of a minimal important difference to infer changes in health-related quality of life [48].

Based on these assumptions, a sample of 181 participants provides > 90% power to detect the following three primary objectives:

(i)superiority of the lifestyle arm versus control for steps per day;(ii)superiority of the lifestyle + sleep arm versus control for steps per day;(iii)superiority of the lifestyle + sleep arm versus control for EQ-5D-5 L.

This design also provides reasonable power for two additional comparisons:

(iv)lifestyle versus control for EQ-5D-5 L;(v)lifestyle + sleep versus lifestyle for EQ-5D-5 L.

Accounting for an anticipated 10% dropout rate, the study will aim to recruit 201 participants.

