#### Analysis of the outcomes

The primary objectives consist in 5 different questions, which are organized in a single hierarchy (see Figure S1) so as to control the overall type I error of the primary objectives at a 5% level. Therefore, to avoid the inflation of alpha risk associated with multiple tests, the next level of the hierarchy will only be tested if the null hypothesis of the previous level is rejected. Primary and secondary outcomes (continuous variables) will be compared between groups using a t-test. Mixed effects linear models will also be used when necessary (repeated measures). The significance level of all tests corresponding to secondary objectives will be set at 0.05. Analyses will be conducted using R software or SAS.

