In conclusion, if the lifestyle and sleep intervention proves to be effective in improving quality of life and increasing physical activity levels, it could have significant implications for public health strategies. The incorporation of sleep into lifestyle interventions may become a crucial component for promoting sustained health improvements, with the potential for broad-scale implementation.

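### The primary objective asks what sleep adds to lifestyle on quality of life and steps; the five primary questions test that contrast on EQ-5D-5L only, and the three with over 90% power are all against control

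*Protocol article*

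**What the plan says.** The Study objectives section gives one primary objective: to "determine whether adding a structured sleep component to a standard lifestyle program improves health-related quality of life and physical activity (step count"). The comparator named there is the lifestyle program without sleep support. The Discussion part of the abstract describes the purpose of the trial in the same way. The Primary outcome section gives both outcomes primary status: "The study has two primary outcomes, assessed 6 months after randomization".

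The Sample size calculations section claims over 90% power, with 181 participants, for three primary objectives:

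- (i) lifestyle against control on steps;
- (ii) "superiority of the lifestyle + sleep arm versus control for steps per day";
- (iii) lifestyle + sleep against control on EQ-5D-5L.

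It then names two additional comparisons, described as having reasonable power, with no figure:

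- (iv) lifestyle against control on EQ-5D-5L;
- (v) lifestyle + sleep against lifestyle on EQ-5D-5L.

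The Analysis of the outcomes section counts all of these as primary: "The primary objectives consist in 5 different questions, which are organized in a single hierarchy". The order of testing is in Figure S1, which is not shown.

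The closing paragraph of the Discussion considers the case in which the combined intervention proves effective, and says: "The incorporation of sleep into lifestyle interventions may become a crucial component for promoting sustained health improvements".

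**The concern.** The objective is a contrast between the two active arms on two outcomes. Only one of the two resulting tests, (v), is among the five primary questions. The steps half has no confirmatory test, although the sample size section assumes a step difference between those arms.

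The tests that carry the stated power answer a different question. Lifestyle + sleep against control contains the whole lifestyle effect, so rejecting that null hypothesis does not show that sleep contributed. Someone who reads the objective and then sees the powered tests succeed could take the result as evidence for adding sleep. The document nowhere says that such a claim must rest on the comparison of the active arms. The count of primary hypotheses also differs between sections, three in one and five in the other.

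**Working it through.** **Inputs (Sample size calculations).** Mean change in steps: "centered at 0 in the control arm, 1800 in the lifestyle intervention arm, and 2200 in the lifestyle and sleep intervention arm", SD 2121. Mean change in EQ-5D-5L: 0, 0.07 and 0.14, SD 0.21. Evaluable N = 181, allocated 1:1:1, so n = 181/3 = 60.3 per arm. The overall type I error is 5% (Analysis of the outcomes). Sidedness is not stated, so two-sided is assumed and one-sided 5% is shown as the range.

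**Formula.** SE = SD × √(2/n), and power ≈ Φ(difference/SE − 1.96), checked with the noncentral t.

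- SE for steps = 2121 × √(2/60.3) ≈ 386.
- SE for EQ-5D-5L = 0.21 × √(2/60.3) ≈ 0.0382.

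**The plan's own figures reproduce.**

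| Test | Difference | Power (normal; t) |
|---|---|---|
| (i) lifestyle − control, steps | 1800 | 99.6%; 99.6% |
| (ii) lifestyle + sleep − control, steps | 2200 | 99.99%; 99.99% |
| (iii) lifestyle + sleep − control, EQ-5D-5L | 0.14 | 95.6%; 95.3% |

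Joint power for (i) to (iii) is about 95% (simulation with 400,000 replicates, shared arms, correlation between outcomes assumed 0 to 0.5). The claim of over 90% is correct. So is the recruitment target: 181/0.9 = 201.1.

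**The contrasts named in the objective.**

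| Contrast, lifestyle + sleep − lifestyle | Difference | Power (normal; t) | One-sided 5% | With 67 per arm (no dropout) | n per arm for 80% |
|---|---|---|---|---|---|
| Steps (not among the five) | 2200 − 1800 = 400 | 17.8%; 17.6% | 27% | 19% | 442 |
| EQ-5D-5L (comparison v) | 0.14 − 0.07 = 0.07 | 44.9%; 44.3% | 57% | 48% to 49% | 142 |

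The 95% CI half-width for the steps contrast, with 60 per arm, is 1.98 × 2121 × √(2/60) ≈ 767 steps, nearly twice the assumed 400.

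**If sleep adds nothing.** Set lifestyle + sleep equal to lifestyle.

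- At 1800 steps in both active arms, (i) and (ii) both succeed about 99.3% of the time.
- At 0.07 in both active arms, (iii) becomes 0.07 against 0, with about 44% to 45% power. Joint success on (i) to (iii) is then about 44% (44.5% to 44.7% in the normal-approximation simulation, slightly less with the t-test).
- At 0.14 in both active arms, (iii) alone has 95.3% to 95.6%. The joint probability is at least 0.953 + 0.993 − 1 = 0.946 and at most 0.956, so about 95%.

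Success on (i) to (iii) therefore cannot separate a sleep effect from a lifestyle effect.

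**The case against.** Four points on the other side have force.

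- **The active arms are compared.** A reader might infer that no primary test isolates sleep. That is not so: (v) is that contrast on EQ-5D-5L, and the count of five places it inside the alpha-controlled hierarchy. The gap is the steps half of the objective and the low power of (v).
- **The comparisons with control serve stated aims.** The Introduction names the combined effect of the three behaviors as the evidence gap, and the Study design section sets out to evaluate all three arms. Testing each active arm against control is not a design fault. The narrow wording of the primary objective does not fit it.
- **A useless sleep component would not be expected to meet all three powered objectives.** That stronger reading is tempting because joint power is about 95%, but that figure assumes that sleep adds 0.07. Under the plan's lifestyle effect of 0.07 and no sleep effect, only (i) and (ii) are expected to succeed.
- **The Discussion sets no decision rule.** Its closing paragraph is conditional and hedged. It does not say that beating control alone counts as effective, so the document does not commit the trial to recommending sleep on that basis.

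Nor can it be said that (v) is the last gate. It is listed last in the text, but the order of testing is in the figure that is not shown. The three-or-five discrepancy is a matter of labeling. None of this supplies the missing steps contrast.

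**Conclusion.** The point holds as a contradiction between the stated primary objective and the confirmatory tests. Lifestyle + sleep against lifestyle on steps is promised as primary and is absent from the five primary questions. On EQ-5D-5L the contrast is present, with about 44% power on the plan's own assumptions. The omitted steps contrast would have about 18%. Every test with over 90% power is against control and cannot isolate sleep.

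The figures rest on the stated means and SDs, about 60 evaluable per arm and a two-sided 5% level. One-sided testing or no dropout raises them somewhat but leaves both contrasts far below 80%. The plan's own power claim for (i) to (iii) and its recruitment target are correct and not in dispute.

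**What to change.** - **Align objective and tests.** Reword the primary objective in Study objectives and in the abstract's Discussion to match the five hypotheses tested. Alternatively, add lifestyle + sleep against lifestyle on steps as the last test of the hierarchy and state its power of about 18%. If it is not added, report it as a secondary estimate with a 95% CI.
- **State the power of (v).** In Sample size calculations, replace the word reasonable with the figure, about 44%.
- **Use one count.** Call either three or five hypotheses primary, in both Sample size calculations and Analysis of the outcomes.
- **Fix the basis for claims about sleep.** State that any conclusion about adding sleep, including the one in the closing Discussion paragraph, rests only on the lifestyle + sleep against lifestyle contrasts.

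The cost is wording and a more modest headline claim. No extra participants are needed. The Data analysis section says that the full analysis plan will be validated before database lock, so this can be settled there.

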## Methods

### Study design

The SleeP exercIse nutRition heALth+ (SPIRAL+) study is a single-centre, three-arm randomized controlled trial (RCT) designed to evaluate the effects of a lifestyle intervention (physical activity and diet), a lifestyle and sleep intervention, and a control condition in non-exercising adults aged 18–80 years. Participants will be recruited through passive methods (advertisements in the community and/or on social media) or active methods (through word of mouth or referral by a health professional). Eligible participants will be randomly allocated (1:1:1) using a computer-generated sequence with concealed allocation. The study is conducted in a *Maison Sport Santé*, located within a teaching hospital in Grenoble, France. Maisons Sport-Santé are national physical activity facilities in France that aim to promote physical activity and healthy lifestyles for the prevention and management of chronic diseases.

The intervention is described according to the TIDieR checklist, and the study protocol follows the 2025 SPIRIT guidelines [28] [see Additional file 1 and Table 1]. The conduct and reporting of the trial will comply with CONSORT 2025 guidelines [29]. Assessments will be performed at baseline, post-intervention and after a 6-month follow-up. For an overview of the study design, see Fig. 1.

**Table 1 Tab1:** Standard Protocol Items: Recommendations for Interventional Trials (SPIRIT) schedule of enrolment, interventions and assessments [28]

TIMEPOINT	STUDY PERIOD					
	Enrollment Pre-study	Visit 1 Baseline t _0_	Visit 2 2 weeks 2 weeks ± 10 days	Visit 3 26 weeks 6 months ± 15 days	Visit 4 52 weeks 12 months ± 15 days	
Enrollment:						
Information	⎫	⎫				
Informed consent		⎫				
Allocation/randomization		⎫				
Interventions:		⎫		⎫	⎫	
Usual Care/Control						
Lifestyle						
Lifestyle + sleep						
Assessments^1^:						
Clinical examination		⎫		⎫	⎫	
Paraclinical examinations		⎫		⎫	⎫	
Notification of adverse events		⎫	⎫	⎫	⎫	
Questionnaires		⎫	⎫	⎫	⎫	
Qualitative interviews				⎫	⎫	

^1^ For the full list of assessments, see outcomes

**Fig. 1 Fig1:**
[figure not shown]
Study design

### Participants

#### Non-inclusion criteria

Participants will be excluded if any of the following apply: EQ-5D-5 L score of 11111.Presence of any condition that in the opinion of the responsible physician or investigator makes the potential participant unsuitable for the study.Diagnosed and treated sleep disturbance (sleep apnea, insomnia, restless legs syndrome) or a sleep consultation conducted within the last year by a sleep specialist (consultation and/or sleep recording via polygraphy or polysomnography).Belonging to populations covered in Articles L1121-5, L1121-6 and L1121-8 of the Public Health Code (pregnancy, person deprived of liberty or subject to a legal protection measure, vulnerable person or legally protected adult).Current participation in another interventional study.

#### Inclusion criteria

Participants are eligible to participate in the study if they meet the following criteria:

Aged 18 to 80 years.Physically inactive, defined as engaging in less than 150 min of leisure-time physical activity per week.Able to provide written informed consent.Able to participate in regular physical activity (no medical contraindication to exercise).Affiliated to the social security system or benefiting from such a system.

### Recruitment procedure

The overall trial flow is outline in Fig. 2. Participants will be recruited through passive methods (advertisements in the community and/or on social media) or active methods (through word of mouth or referral through a health care professionals). Community-based recruitment strategies will be employed (local newspapers, radio stations, flyers in medical and paramedical waiting rooms, pharmacies, teaching hospitals, newsletters and contact with potential referral sources). Recruitment started on May 2nd 2024.

